### Objectives

The objective of this RCT is to evaluate the effectiveness of the BCS program for Chinese women with breast cancer undergoing chemotherapy in terms of enhancing the women’s self-efficacy, social support and QoL, and reducing their symptom distress, anxiety and depression.

We hypothesise that compared with the control group at baseline, post-test 1 and post-test 2, the women with breast cancer who are undergoing chemotherapy in the experimental group will have the following significant differences:

1. Improved self-efficacy, social support and QoL;

2. Reduced symptom distress, anxiety and depression; and

3. Greater satisfaction with the health care received during chemotherapy.

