### Participant timeline

This study began recruiting participants in May 2016, and the primary endpoints (baseline and post-test 1) and follow-up measure (post-test 2) are expected to be completed in February 2017. The Consolidated Standards of Reporting Trials (CONSORT) flowchart is presented in Fig. 3 [38].

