### Sample size

The primary outcome of self-efficacy will be used to estimate the effect size based on power analysis [39]. A previous study on IIPs for women with breast cancer that measured QoL, social support, and health competence reported a medium effect size (0.46); however, the effect size for self-efficacy was not mentioned [40]. Similar research on psychoeducation to enhance the self-efficacy of Chinese patients with colorectal cancer also demonstrated a medium effect size of 0.60 for self-efficacy [29]. We estimate a 20% attrition rate based on a dropout rate of 10–15% in previous studies involving IIPs [27, 40]. To achieve a power of 0.80 at a 0.05 level of significance, a minimum of 108 women (54 in each group) are required for this study.

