### Recruitment

Recruitment will take place before the women begin chemotherapy. The physician will introduce the BCS to women who meet the inclusion criteria and will provide the women with the contact details of the research assistant (RA). Women that have contacted the RA will be approached by the RA at the oncology unit to provide them with additional information regarding the BCS and to answer any questions that they might have. Women who verbally agree to participate will be followed up to obtain their written consent. The enrolment period is expected to extend over a 6-month period. Data will be collected before randomisation (baseline), immediately after the intervention (post-test 1), and 12 weeks after the intervention (post-test 2). The women will be rewarded with a small gift (equal to RMB 30) for each questionnaire completed.

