### Data analysis

All outcome measures will be analysed using IBM SPSS Statistics 21.0 [42]. An intention-to-treat analysis will be adopted to manage missing data. The baseline differences between the intervention and control groups will be assessed using the chi-square (χ^2^) test for binary demographic data and the independent sample t-test for continuous variables. Adjusted for possible confounding factors of demographic variables, the repeated measures triply MANCOVA will be conducted to determine whether the BCS intervention is effective in improving self-efficacy, social support and QoL and for reducing symptom distress, anxiety and depression across three time points of data collection (baseline, post-test 1 and post-test 2). The independent t-test will be used to compare how satisfied the experimental group and the control group are with the care that they received during chemotherapy 12 weeks after intervention.

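### Baseline is analysed as an outcome time point and not named as a covariate, which gives up precision, and the hypothesis and primary endpoints are worded to include this pre-randomisation visit

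*Protocol article*

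**What the plan says.** Four sections of the protocol article bear on the point.

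- **Data analysis.** The plan states that "the repeated measures triply MANCOVA will be conducted to determine whether the BCS intervention is effective", and the comparison runs "across three time points of data collection (baseline, post-test 1 and post-test 2". The adjustment is described as "Adjusted for possible confounding factors of demographic variables". The baseline score of the outcome scale is given a role as an outcome and is not named as a covariate. The section does not say whether the group main effect or the group-by-time interaction answers the question.
- **Objectives.** The hypothesis is that the experimental group will differ significantly "compared with the control group at baseline, post-test 1 and post-test 2".
- **Participant timeline.** Baseline is grouped with the first follow-up as "the primary endpoints (baseline and post-test 1", and post-test 2 is the follow-up measure.
- **Recruitment.** "Data will be collected before randomisation (baseline", followed by post-test 1 immediately after the intervention and post-test 2 twelve weeks after it.

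**The concern.** Under randomisation the expected group difference at a pre-randomisation visit is zero. A hypothesis of a difference there cannot be true by design, and such a visit cannot be an endpoint for the intervention. Because the same idea appears in the hypothesis, the timeline and the analysis, it could carry through into how the model is fitted and read.

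Power is what is at stake. The baseline score of the same scale is usually the best available predictor of the follow-up score. Used as a covariate, it removes variance from the treatment comparison. Used as a third outcome visit, it either enters the group mean with zero effect (main effect) or serves as a reference whose own variance is added to the comparison (interaction). The trial is planned for power 0.80 with 108 women, so the choice can decide whether that level is reached.

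**Working it through.** **1. The plan's own figure.** The Sample size section gives 54 per group, power 0.80, level 0.05 and 20% attrition. It cites two effect sizes: an earlier internet programme "reported a medium effect size (0.46" for other outcomes, and a psychoeducation study that "also demonstrated a medium effect size of 0.60 for self-efficacy". An exact two-sided t-test at one visit with d = 0.60 needs 45 per group, and 45 × 1.2 = 54, total 108. So 108 corresponds to a single-visit comparison and does not depend on how baseline is handled. Two-sidedness is my assumption.

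**2. Inputs for the comparison.**
- Completers per arm: n = 54 × 0.8 = 43.2, taken as 43.
- Effect: 0 at baseline (Recruitment section), d = 0.60 SD at both post-tests. That it is equal at both post-tests is an assumption.
- Correlation r, equal between all visits. The documents give no value; 0.3, 0.5 and 0.7 are assumed.
- One outcome, no demographic covariates, two-sided 0.05.

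**3. Formulas.**
- *Group main effect over three visits.* The mean effect is (0 + 0.60 + 0.60)/3 = 0.40, two thirds of 0.60. The variance of a three-visit mean is (1 + 2r)/3. The standardised effect is 0.40/√((1 + 2r)/3).
- *Group-by-time, 2 df.* A Hotelling test on the two changes from baseline. The squared distance is 2d²/(3(1 − r)) for a sustained effect and d²/(2(1 − r)) if the effect halves by post-test 2. Noncentrality is n/2 times that, with F on 2 and 83 df.
- *ANCOVA at post-test 1.* The standardised effect is 0.60/√(1 − r²).

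At r = 0.5 the main effect is 0.40/√0.667 = 0.49. The interaction distance is 0.72/1.5 = 0.48, noncentrality 21.5 × 0.48 = 10.3. The ANCOVA effect is 0.60/√0.75 = 0.69.

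**4. Power.**

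| Test | r = 0.3 | r = 0.5 | r = 0.7 |
|---|---|---|---|
| Group main effect, three visits | 0.71 | 0.61 | 0.54 |
| Group-by-time, sustained effect | 0.66 | 0.81 | 0.96 |
| Group-by-time, effect halves by post-test 2 | 0.53 | 0.69 | 0.90 |
| ANCOVA at post-test 1 | 0.82 | 0.89 | 0.97 |

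For reference, a t-test at one post-test that ignores baseline has power 0.785 with 43 per arm.

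**5. A like-for-like comparison.** The interaction uses both post-tests, so it is fairer to set it against ANCOVA on their mean, for which power is 0.957/0.973/0.996. Its information relative to the main effect is 3/(2(1 − r)), that is 2.1/3.0/5.0. Relative to the interaction's noncentrality it is 3/(1 + 2r), that is 1.87/1.50/1.25.

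**6. Sensitivity to the effect size.** With d = 0.46 at both post-tests, power at r = 0.3/0.5/0.7 is 0.486/0.406/0.349 for the main effect, 0.432/0.573/0.805 for the interaction and 0.599/0.682/0.839 for ANCOVA at post-test 1. ANCOVA is again the most powerful. At r = 0.8 the last two almost meet (0.938 and 0.940).

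**The case against.** The strongest reply is that the article does not commit to the main effect. The Trial design section describes a pre-test with repeated post-tests, and the usual test for that layout is group-by-time. There baseline is the reference, nothing is diluted and the type I error is kept. A reader might infer from the three-visit wording that the planned test is diluted. The document does not support that as an unconditional statement, because dilution follows only if the main effect decides. Naming the contrast may also have been left to a fuller document. This part of the reply stands.

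Four further points need weighing.

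- *Size.* From r of about 0.5 with a sustained effect, the interaction reaches the planned 0.80, and at r = 0.7 it is within about one point of ANCOVA. This stands. At lower r, or if the effect fades, the gap is material.
- *Model.* The planned analysis is multivariate with demographic covariates, and the figures are for one outcome without them. They illustrate the principle and are not this trial's power.
- *Wording.* The Objectives may simply list measurement occasions, and the timeline sentence is about completion dates. A reader might infer that an intervention effect at baseline is expected. Nothing else supports this, since baseline differences are checked separately in the Data analysis section. The wording still says something that randomisation rules out.
- *Estimates.* It would be too strong to say that the planned model cannot give a difference at post-test 1. A fitted repeated measures model can. As described, that difference would not be adjusted for the baseline score.

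What the reply does not answer is that the role given to baseline is stated in the article: it is an outcome time point, and the named adjustment is for demographic variables.

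**Conclusion.** The point holds as one of efficiency and wording. Baseline is placed among the outcomes and is not named as a covariate, and two other sections word it as a hypothesised difference and a primary endpoint.

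The cost depends on the effect that decides. Under the main effect it is large: every value in the assumed range is below both the planned 0.80 and the 0.785 of a single-visit t-test. Under the interaction it runs from 16 points of power at r = 0.3 (0.66 against 0.82) to about one point at r = 0.7 with a sustained effect. Over r = 0.3 to 0.7, ANCOVA at post-test 1 has the highest power of the tests tabulated. This rests on an assumed correlation, equal correlation across visits, and a single outcome.

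Two stronger conclusions are not supported. The planned analysis is not invalid or biased by including baseline. Nor does the point justify making SICPA the only primary result, because the Primary outcomes section lists MSPSS as well.

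**What to change.** - In the Objectives, remove baseline from the time points at which a group difference is hypothesised.
- In the Participant timeline, remove baseline from the primary endpoints.
- In the Data analysis section, take post-test 1 and post-test 2 as the outcomes, with the baseline value of the same scale as covariate. A model that keeps baseline in the outcome vector but constrains the group means there to be equal would also serve.
- Name the decisive contrast: the baseline-adjusted group difference at post-test 1, with its 95% CI, for each primary outcome (SICPA and MSPSS). Give post-test 2 as the follow-up contrast.

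Only wording and model specification change. The baseline scores are already collected and the sample size of 108 is unaffected, so there is no cost in patients or procedures.

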### Ethics, consent and permissions

The ethics approval for this study has been obtained from the Human Research Ethics Officer at the University and the participating hospitals. This study will adhere to ethical standards for the whole procedure. Women will not be deprived of any treatment and routine care, and there is no potential rick or harm by participating in this program. Women will be assured that participation in this study is voluntary and they can withdraw from the study at any point of time without any effect on their treatment. The consent form will be obtained and all data will be kept confidential and anonymous.

## Discussion

This study will contribute to evidence on the effectiveness of using a theory-based BCS program to support women as they cope with the unique challenges of breast cancer and chemotherapy. The results of this study will provide a better understanding of the role of self-efficacy and social support in reducing symptom distress and the credibility of using a theoretical framework to develop a BCS intervention. Such knowledge may help to advance research regarding the use of internet-based interactive methods to promote women’s symptom self-management, thus improving women’s QoL and psychological well-being.

If the BCS program is effective, it could be offered by health care professionals as part of the routine treatment to enhance health outcomes for women with breast cancer who are undergoing treatment in China. The knowledge gained from this study could be used to plan a culturally appropriate BCS program for other cancer patients. If the BCS program is effective, this study will provide evidence to support the need to train staff in e-health and to allocate resources for developing e-health to further advance this effort. To the best of the researchers’ knowledge, this is the first study of its kind that evaluates a BCS intervention using a rigorous research design and a theoretical framework in China.

## Abbreviations

APP: Mobile application
BCS: Breast Cancer e-Support
FACT-B: Functional Assessment of Cancer Treatment-B
HADS: Hospital Anxiety and Depression Scale
MDASI: M.D. Anderson Symptom Inventory
MSPSS: Multidimensional Scale of Perceived Social Support
RA: Research assistant
RCT: Randomised controlled trial
SICPA: Stanford Inventory of Cancer Patient Adjustment
